### Step 3: study selection

After checking the titles and abstracts of all articles, the full text of the studies will be evaluated to identify the articles that met the inclusion criteria. All observational, and interventional studies, and programs will be assessed based on the needs, recommendation and strategies for self-efficacy promotion of teen mother during postpartum period.

### Step 4: charting the data

After finding the full texts of relevant articles, data of each article including the author's name, publication date, type of studies, setting, the sample size, intervention development, the time of the interventions, measurement tool, the needs, recommendation and strategies for promoting self-efficacy of teen mother, and main findings will be extracted using a structured form. Using the results of a scoping review, the needs, solutions and strategies for improving the self-efficacy of teen mothers will be extracted.

### Step 5: collating and summarizing of result

In this step, the quantitative and qualitative information of each relevant article will be analyzed separately by two reviewers.

#### The third phase: designing a postpartum self-efficacy promotion program

In this stage of the research, after extracting the self-efficacy needs of teen mothers through qualitative study and scoping review, the decision matrix will be used to prioritize the strategies. In the first round of Delphi, a number of specialists (including obstetricians, reproductive health experts, child psychologist, maternal health policymakers, youth health policymakers) will assign to each proposed strategy a score of 1 to 9 based on four criteria including cost, time spent, place of implementation and feasibility. A score of 9 corresponds to the option “It is expected benefits are greater than its harms” and a score of 1 is related to the option “It is expected harms are much greater than its benefits”. The average score for each question will be obtained, if the score is between 1 and 3, it will be considered as an inappropriate option and will be removed from the program. Scores from 7 to 9 will be entered into the program as suitable options, and scores from 3 to 7 will be entered into the second round of Delphi to achieve general consensus.

In the second round of Delphi, experts will be invited again to attend the face to face meeting to discuss the prioritization of strategies, the components of the program, its structure and application, the team members involved in it and other points of disagreement in the first Delphi phase. In the end, based on the panel members’ views, Comments and suggestions will be collected and applied to the design of the intervention program, and subsequently finalized and implemented in the quantitative phase.

## The fourth phase: quantative phase

### Type of quantitative study

The quantitative phase of the research will be carried out using a two-group semi-experimental study.

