### Sampling method, and sample size

The sample size will be calculated using a pilot study. The sampling will be conducted by convenience and non-probabilistic sampling methods. The researcher by referring to the research environment on consecutive days will choose the number of teen mothers who have inclusion criteria in the easy method. Thereafter, participants will assign to the intervention and control groups based on ALLOCATION and RANDOM software. The sample size will be calculated based on pilot study.

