### The implementation method

Based on the opinion of expert panel, a part of the strategies and goals will be determined in the form of an intervention program. After approving the protocol of the study with Ethics Committee, and obtaining the necessary coordination between the authorities of healthcare centers and hospitals, the researcher will implement the designed interventional program. After explaining the aim of the study (by [name]), verbal, and informed consent will be given from the eligible women, and if they agree, they will enter the study and be randomly divided into two groups. For sampling, eligible women will be entered into the study using the convenience sampling method. Then, for randomized assignment, the women will randomly assign either to the trial or control groups based on the table of random numbers that will be generated by Random Allocation Software 2.0. To prevent selection bias, allocation concealment to the trial or control group will be done by a researcher who does not participate in the data collection ([name]).

At first, in the 36th week of pregnancy, a pre-test will be taken from both groups and the average self-efficacy scores will be compared between the two groups. The intervention group received the self-efficacy promotion program and the control group did not receive any intervention. After delivery, their self-efficacy score will be checked between two groups. The type of intervention (e.g., role playing, peer education, home visit, virtual training, and etc.), the time of the program implementation (pregnancy, after childbirth, etc.), the people involved in the program will be determined based on the opinion of the expert panel.

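### The quantitative phase is labelled semi-experimental although women are allocated at random; correct the label and make the primary analysis keep every randomised woman in her allocated arm

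*Protocol article*

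**What the plan says.** All references are to the protocol article, fourth phase.

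- **Type of quantitative study.** The only formal statement of the design is: "The quantitative phase of the research will be carried out using a two-group semi-experimental study".
- **Sampling method, and sample size.** Recruitment is non-random: "The sampling will be conducted by convenience and non-probabilistic sampling methods". Allocation comes next, as a separate step: "Thereafter, participants will assign to the intervention and control groups based on ALLOCATION and RANDOM software".
- **The implementation method.** Of consenting women it says that "they will enter the study and be randomly divided into two groups". It then describes the sequence, a random-number table from Random Allocation Software 2.0, and adds that "allocation concealment to the trial or control group will be done by a researcher who does not participate in the data collection". Both groups take a pre-test at 36 weeks. Controls receive no intervention, and self-efficacy is measured again after delivery.
- **Exclusion criteria.** Three grounds are listed: no longer wishing to take part, a high-risk obstetric event, and not having received half of the intervention, whatever the reason.
- **Objectives.** The aim of this phase is to determine the effect of the programme on the self-efficacy score.

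**The concern.** A semi-experimental (quasi-experimental) study ordinarily forms its groups without randomisation. A generated random sequence, assignment of individuals from it and concealment of the allocation are the defining elements of a randomised trial. The declared design and the described procedure therefore do not match, and no sentence in the article explains the label.

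The design is also what tells a reader which analysis to expect. Under randomisation the natural primary comparison is between all women allocated to each arm, because that comparison carries the protection that random allocation provides. The exclusion criteria cut across it by removing women for things that happen after allocation, and one of the three grounds can affect one arm only. With the design mislabelled, nothing in the text signals that these removals weaken a randomised comparison.

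**Working it through.** No arithmetic applies. The article states no sample size (it defers this to a pilot study), no power and no expected attrition. The check is a comparison of the sections.

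1. **How do women enter the study?** By convenience sampling, in the sections on the research sample, on sampling and on implementation. This bears on whom the results apply to.
2. **How do women reach an arm?** The sampling section uses allocation software without the word randomly. The implementation section is explicit: "the women will randomly assign either to the trial or control groups based on the table of random numbers that will be generated by" the named software. Both point to individual random allocation, and no section describes any other way of forming the groups.
3. **Is the allocation protected?** Yes. Concealment is assigned to someone outside data collection.
4. **Does step 1 explain the label?** No. The sampling section places allocation after recruitment, so the two are distinct. A non-random sample limits generalisability but does not turn a randomised comparison into a quasi-experimental one.
5. **Where is the error?** In the one sentence that names the design. The procedure is consistent with itself, and the data collection section also calls this phase a trial.
6. **What follows for the exclusions?** The implementation section has consent and random division into groups, with the programme following. Dropping out, a later obstetric event and under-receipt of the programme therefore arise after allocation or can do so. Taking each ground in turn:
   - *Under-receipt of the programme.* Controls are given no programme, so no control can be removed for under-attending it. This ground can only take women out of the intervention arm.
   - *Unwillingness to continue.* It can occur in both arms, but the demands on the two arms differ, so equal losses cannot be assumed.
   - *High-risk obstetric event.* It can occur in both arms. It is still known only after enrolment, so removing these women also leaves fewer than were randomised.
7. **Direction.** If women who under-attend would also tend to score lower, removing them from one arm only makes the programme look better than it is. That link is an assumption; the article has no data on it. The asymmetry itself follows from the text.

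**The case against.** The strongest reply is that this is one wrong word. Every sentence on how women reach an arm describes randomisation, so staff following the article would randomise, and changing the label alters no allocation, measurement or listed test. On that view it is a minor wording correction. It can be added that per-protocol exclusions also occur in randomised trials and form a separate matter, and that a condensed article may leave analysis sets to a fuller document.

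Much of this stands. Three stronger readings that a reader might infer should not be made:

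- *That the design sentence would lead to non-random grouping.* It contains no allocation rule, and the explicit procedure elsewhere governs.
- *That comparing pre-test means shows a non-random design.* Baseline comparisons are common in randomised trials.
- *That a quasi-experimental study could support only an association.* Such designs can support causal estimates, though on stronger assumptions.

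Nor does the article make conflicting statements about its conclusions. It has a single objective, the effect of the programme.

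What does not stand is that nothing beyond wording is involved. The exclusions are stated in the article, so this is not a detail left to another document. Calling the study what it is, a randomised trial, makes them questionable as a rule for the primary analysis. Their occurrence in other trials supports a secondary per-protocol analysis, not a primary one.

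**Conclusion.** The point holds in a limited form. The design label is wrong for the procedure planned, and correcting it should bring the primary analysis into line with random allocation. The label error has no effect on conduct; its cost is in how the study is classified and reported. The post-allocation exclusions carry the real risk of bias. Their size cannot be given, because it depends on how many women under-attend or stop and how their scores differ, and the article reports neither.

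This rests on two assumptions. The first is that the sponsor means to randomise, as the implementation section says; if non-random groups were intended, the allocation text would have to change instead. The second is that exclusion means removal from the analysis. The section does not say whether it means that, the end of follow-up, or both.

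**What to change.** 1. In the section on the type of quantitative study, describe a two-arm, parallel-group, individually randomised controlled trial in a convenience sample. Confine the convenience-sampling caveat to generalisability.
2. State that the primary analysis includes all randomised women in the arm to which they were allocated.
3. In the exclusion criteria, make clear that events after allocation do not define the primary analysis set. They may define a secondary per-protocol analysis, labelled as such.
4. Seek the post-delivery questionnaire from women who stop the programme or under-attend, as far as they agree to give it.

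**Cost.** One sentence on design, a clarification of the exclusion criteria with the analysis statement that goes with it, and some extra follow-up effort. Allocation does not change. The estimated effect may be somewhat smaller, because women who received little of the programme stay in its arm.

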### Research population

The targeted population is all adolescent mothers referred to health care centers affiliated to Isfahan University of Medical Sciences.

### Research sample

The study sample will be formed from a group of teen mothers who will be selected by convenience sampling method and have all inclusion criteria for the study.

### Research environment

This study will be carried out in selected comprehensive health care centers, obstetrics and gynecology offices, perinatal clinics of hospitals and all places where teen mothers are accessible. The reason for choosing such kind of environment is easy access to teen mothers and includes the majority of cultural and social classes. Considering that the present research is a mixed method study, the type and time of the intervention will be determined based on the findings of the previous stage, but our prediction is that the intervention will start from pregnancy.

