### Inclusion criteria

Pregnant women aged between 15 and 19 years, pregnancy age over 36 weeks, low-risk singleton pregnancy, Iranian citizenship, consent to participate in the study, not having history of any diagnosed mental or chronic diseases undergoing drug treatments, and ability to read and write.

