### Exclusion criteria

Unwillingness to continue cooperation during the study, occurrence of high-risk obstetric conditions (e.g., pre-eclampsia, premature birth, hysterectomy, etc.), failure to receive 50% of the intervention for any reason.

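### The open-ended entry criterion (over 36 weeks), the week-36 pre-test, the predicted start in pregnancy and the 50% receipt exclusion are not reconciled

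*Protocol article*

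**What the plan says.** All four statements are in the fourth-phase part of the protocol article.

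- **Inclusion criteria:** "Pregnant women aged between 15 and 19 years, pregnancy age over 36 weeks, low-risk singleton pregnancy". No upper gestational limit is given.
- **The implementation method:** "in the 36th week of pregnancy, a pre-test will be taken from both groups". The intervention group then receives the programme, the control group receives nothing, and self-efficacy is measured again after delivery. When the programme runs (before or after birth) is left to the expert panel.
- **Research environment:** "the type and time of the intervention will be determined based on the findings of the previous stage, but our prediction is that the intervention" is to begin before birth.
- **Exclusion criteria:** these include "failure to receive 50% of the intervention for any reason", and also premature birth.

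Sampling method, and sample size adds that the researcher visits the sites on consecutive days and enrols eligible women by convenience.

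**The concern.** The entry window is already fixed, but the programme it must accommodate is not, and the article does not say that the window will be revisited. Convenience enrolment of whoever meets the criteria will bring in women at different points after 36 weeks. If the programme has an antenatal part, how much of it a woman can receive then depends partly on when she happened to be approached.

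Two things are at stake. Women with little exposure may stay in the analysis, which pulls the estimated effect towards zero. Or the 50% rule may remove them after randomisation, and then the arms are no longer the groups that were randomised. Controls have no programme to fall short of, so this loss can occur only in the intervention arm.

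**Working it through.** **1. Entry against pre-test.** Eligibility is any gestation above 36 weeks. The most generous reading of the 36th week is 36+0 to 36+6. The two agree only for women entering in those seven days. A woman entering at 37, 38 or 39 weeks meets the criterion, but the stated pre-test time has passed.

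**2. Time left before birth.** The article gives no gestation distribution, entry pattern, session count or programme length, so there is no figure of its own to reproduce. What follows is illustrative.

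Assume gestation at birth G is normal with mean μ of 38.5 to 39.5 weeks and SD σ of 1.2 to 1.5, cut at 42.3 weeks. Births before 37 weeks are dropped because premature birth is an exclusion. With F the normal distribution function, for a woman still pregnant at entry week e:

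P(t weeks or less left) = [F(e + t) − F(max(e, 37))] / [F(42.3) − F(max(e, 37))]

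Worked case with μ = 39, σ = 1.2, t = 2:

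- Entry at 38: (0.798 − 0.202) / (0.997 − 0.202) = 0.75.
- Entry at 36: (0.202 − 0.048) / (0.997 − 0.048) = 0.16.

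Over the whole assumed range:

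| Entry (weeks) | Median weeks left | 2 weeks or less | 1 week or less |
|---|---|---|---|
| 36 | 2.7–3.5 | 9–26% | 0% (by construction) |
| 37 | 1.7–2.5 | 33–62% | 9–26% |
| 38 | 1.0–1.7 | 58–84% | 26–49% |
| 39 | 0.6–1.2 | 79–95% | 44–69% |

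For entry spread evenly over weeks 36 to 40 among undelivered women (μ 39.0 to 39.5, σ 1.2 to 1.3), the median time left is 1.6 to 2.0 weeks. Between 24 and 30% have 1 week or less, and 51 to 60% have 2 weeks or less. Dropping births before 37 weeks barely changes this (23 to 30% and 51 to 60%). With even entry over weeks 36 to 42 and the wider range of μ and σ, 55 to 69% have 2 weeks or less.

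**3. When the 50% rule would bite.** Let a be the share of the programme given before birth and f the part of that share a woman receives. If she attends everything after birth, she receives a·f + (1 − a). This is below 0.5 when f < 1 − 0.5/a.

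- a = 0.5 or less: never triggered by lost antenatal sessions alone.
- a = 0.75: triggered if f is below 1/3.
- a = 1: triggered if f is below 1/2.

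So early birth alone leads to exclusion only if more than half of the programme is antenatal. With a smaller antenatal share, she stays in unless she also misses later sessions, and the consequence is lower exposure. The article does not fix a, so both outcomes remain possible.

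**The case against.** The strongest reply is that the week-36 pre-test shows entry is meant to happen near week 36. On that reading most women have about 3 weeks left, and the figures for even entry do not apply. This is a fair inference about intent and it limits the size of the problem. But eligibility is governed by the inclusion criterion, which has no upper end, and recruitment takes eligible women as they are found. The reply therefore confirms that the two statements need aligning.

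A second reply is that an exploratory sequential design properly leaves the programme to the third phase, and that a condensed article may leave the visit schedule to a fuller document. That stands for the missing programme details, which are not criticised here. It does not cover the entry window, pre-test week and exclusion rule, which the article does state and which disagree.

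A reader might go further and infer that the antenatal part cannot be delivered or tested as designed, or that the trial will be diluted towards no effect. The article does not support either. No antenatal part, session count or length exists yet. A start in pregnancy is only predicted, and starting in pregnancy does not mean finishing in it. Delivery after birth remains open. Dilution is not the only outcome either, since the 50% rule could remove the very women who would cause it, with bias of unknown direction.

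**Conclusion.** The point holds as an unreconciled set of provisions. Following the entry criterion as written admits women who cannot have the stated pre-test. If an antenatal part is adopted, it also admits women who may receive little of it and who could be excluded from the intervention arm alone.

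The size depends on assumptions that the article neither gives nor contradicts. The median time left is about 3 weeks (2.7 to 3.5) for entry at week 36. Half or more of women have 2 weeks or less if entry is even over weeks 36 to 40. Whether either is too short cannot be judged until the programme's length is known. If the whole programme falls after birth, the exposure problem disappears and only the mismatch between entry and pre-test remains. The matter should be settled before recruitment, because it cannot be repaired once women are enrolled.

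**What to change.** After the third phase and before fourth-phase recruitment, reconcile the four statements:

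- Set one gestational entry window, with an upper limit, that agrees with the pre-test timing and leaves room for any antenatal part of the final programme. The limits should follow from that programme's length; none is proposed here.
- If the panel places the whole programme after birth, keep the present window, align the pre-test wording with it, and delete the prediction of a start in pregnancy.
- Record gestation at entry and the sessions each woman received before and after birth.
- State that women whose antenatal sessions were cut off by birth stay in the analysis in the arm to which they were randomised.

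The cost is a few sentences of text and two recorded items. Some women who present late become ineligible and recruitment is slightly slower.

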### Sampling method, and sample size

The sample size will be calculated using a pilot study. The sampling will be conducted by convenience and non-probabilistic sampling methods. The researcher by referring to the research environment on consecutive days will choose the number of teen mothers who have inclusion criteria in the easy method. Thereafter, participants will assign to the intervention and control groups based on ALLOCATION and RANDOM software. The sample size will be calculated based on pilot study.

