### Study variables

In this study, the designed interventions are considered as an independent variable, and postpartum self-efficacy is considered to be the dependent variable. Variables affecting self-efficacy will be determined using different constructs of Bandura’s self-efficacy theory (e.g., including successful experiences of the individual, social modeling, social persuasion, and psychological responses), and based on the results of a qualitative study and scoping review, different areas of self-efficacy (e.g., self-efficacy in self-care, infant care, breastfeeding, etc.) will be determined.

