### Data collection method

Researcher-made questionnaires evaluating postpartum self-efficacy in adolescent mother will be applied in the quantitative phase of this trial. After qualitative interview and searching in existing questionnaire, the validity and reliability of this questionnaire will be determined. In order to assess the content and face validity, the scale will be given to 15 faculty members of the midwifery, gynecology, and psychology department, and their expert’ opinions will be qualitatively received and the suggested changes will be applied in the questionnaire. In order to check face validity, the questionnaire will be provided to a number of women with the characteristics of the research units. The reliability of the tool will be done by test–retest method and the internal correlation will be evaluated with Cronbach’s alpha test.

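### The sample size rests on a pilot study alone, with no target difference named, so the plan permits sizing on the pilot's own effect, which would control power poorly

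*Protocol article*

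**What the plan says.** Under Sampling method, and sample size, the protocol article states the basis of the calculation twice: "The sample size will be calculated using a pilot study" and, at the end of the same paragraph, "The sample size will be calculated based on pilot study". It does not give the size of the pilot, say whether the pilot has two arms, or say which quantity is taken from it. No target difference appears anywhere in the article.

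Three other sections bear on the point:

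- Study variables: "postpartum self-efficacy is considered to be the dependent variable".
- Data collection method: "Researcher-made questionnaires evaluating postpartum self-efficacy in adolescent mother will be applied in the quantitative phase of this trial". The instrument has still to be built and tested for validity and reliability, so the article can give no SD or important difference on it.
- The implementation method: a pre-test is taken in both groups in the 36th week of pregnancy and self-efficacy is scored again after delivery. On allocation, "the women will randomly assign either to the trial or control groups based on the table of random numbers".

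The tests listed under Data analysis do not include ANCOVA.

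**The concern.** A sample size for comparing two means needs a difference to detect and an SD. The article names one source, the pilot, and excludes neither quantity from it. On a new scale, the pilot's observed difference is the only estimate of the effect whose use in sizing the article mentions.

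A pilot can give a usable SD. It estimates a difference between groups much less precisely, and the required size depends on the inverse square of that difference. A pilot that happens to overstate the effect produces a trial that is too small. One that understates it produces an unreachable size, and one that points the wrong way leaves nothing to plan on. The trial report could then state a nominal 80% power that the trial never had.

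**Working it through.** The article states no sample size, power, significance level, difference or SD, so there is no figure to reproduce. The check asks what happens to true power if the pilot effect is used.

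**Inputs.** From the article: two randomised groups, a self-efficacy score as outcome, and a pilot as the basis of the size. Assumed: 1:1 allocation, two-sided alpha 0.05, intended power 80%, SD 1 (standardised scale), true difference d = 0.5 with 0.3 and 0.8 as a range, and a pilot of 10 to 50 per arm.

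**Formulas.** Size per arm: n = 2(1.96 + 0.8416)²/d² = 15.70/d². True power at that size: Φ(d_true × √(n/2) − 1.96).

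**Reference.** With d = 0.5, n = 15.70/0.25 = 62.8, so 63 per arm.

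**Single pilots, true d = 0.5.**
- Pilot d of 0.8: n = 15.70/0.64 = 24.5, so 25 per arm. Power = Φ(0.5 × √12.5 − 1.96) = Φ(−0.19) = 42%.
- Pilot d of 1.0: 16 per arm, power 29%.
- Pilot d of 0.3: 175 per arm, power 99.7%.

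**How often power falls below 50%.** This needs 0.5 × √(n/2) < 1.96, that is n < 2 × 3.92² = 30.7. That corresponds to a pilot d above √(15.70/30.7) = 0.715, so overstating the effect by 0.215 is enough. The standard error of the pilot d is about √(2/m + d²/(4m)) with m per arm. For m = 15 it is 0.371, so the chance is P(Z > 0.215/0.371) = P(Z > 0.58) = 0.281. Dividing by the 0.911 chance of a favourable direction gives 31%.

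**Simulation.** 100,000 pilots per row, true d = 0.5, pilot effect and pooled SD both used. All columns except the last are among pilots in the favourable direction.

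| Pilot per arm | n per arm, 10th–90th percentile | True power, 10th–90th percentile | Power below 50% | Wrong direction |
|---|---|---|---|---|
| 10 | 12–664 | 0.23–1.00 | 37% | 13% |
| 15 | 15–590 | 0.28–1.00 | 31% | 8.6% |
| 20 | 18–522 | 0.32–1.00 | 27% | 5.6% |
| 30 | 22–386 | 0.38–1.00 | 21% | 2.7% |
| 50 | 27–255 | 0.45–1.00 | 14% | 0.6% |

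The hand calculation gives 37%, 31%, 27%, 21% and 15% for the fourth column, in agreement.

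**Sensitivity to the true effect.** With true d = 0.3 and 15 per arm, power runs from 0.17 to 1.00 (10th to 90th percentile). With true d = 0.8 and 50 per arm it runs from 0.56 to 0.99, and 6% of favourable pilots fall below 50%.

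**Pilot used for the SD only, difference fixed at 0.5.** True power runs from 0.64 to 0.91 with 15 per arm, 0.70 to 0.88 with 30, and 0.72 to 0.86 with 50. The corresponding n per arm is 43–86, 49–79 and 52–75. Some spread remains, but it is much smaller.

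**Cost of a conservative SD.** Using the upper 80% confidence limit multiplies n by df/χ²(0.20; df). With df = 18, 28 and 38 (10, 15 and 20 per arm) the factors are 1.40, 1.30 and 1.24. ANCOVA multiplies n by 1 − ρ². At an assumed ρ of 0.5 this is 0.75, giving net factors of 1.05, 0.97 and 0.93. Break-even is at ρ = √(1 − 1/1.40) = 0.53 for 10 per arm and √(1 − 1/1.24) = 0.44 for 20.

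**The case against.** The strongest reply is that the article never says the pilot's effect will be used. Estimating an SD on a new scale is an ordinary purpose of a pilot, and the wording fits that equally well. A reader might infer that the plan commits to sizing on the pilot effect and that its power would be close to arbitrary. The text does not support that. It leaves the quantity open, and the size of the harm depends on an assumed pilot size and true effect.

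Nor is the pilot necessarily the only source of a difference. The scoping review will chart the measurement tools and main findings of earlier studies, and it could inform a standardised difference before the trial is sized.

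Deferral also follows from the design. The questionnaire, the content of the intervention and its timing are all still to be determined, so no difference in scale points can be given now. A journal article may properly leave significance level, power and dropout allowance to the full protocol, and those gaps are not counted here.

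All of this stands, and it makes the point conditional. It does not remove it. The article does not simply stay silent or defer: it names a basis for the size, twice, and that basis is unsuitable for one of the two quantities the calculation needs. Nothing in the text steers away from the poor use, and neither the scoping review nor the expert panel is linked to the sample size.

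**Conclusion.** The point holds as a conditional weakness that should be corrected before the pilot starts. The plan permits, but does not prescribe, sizing on the pilot effect. If that route is taken, then under a true d of 0.5, 80% intended power, two-sided 5% significance and 1:1 allocation, roughly one favourable pilot in three (10 to 15 per arm) to one in seven (50 per arm) leads to a trial with less than 50% true power. A larger true effect reduces the risk, and a smaller one raises it. If the pilot supplies only the SD against a difference fixed in advance, the problem does not arise in this form. Confidence is moderate, because the pilot size, the true effect and the intended use of the pilot are not in the article and the full protocol is not shown.

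**What to change.** Amend the paragraph under Sampling method, and sample size as follows.

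1. Fix the target difference before the pilot. It can be the smallest important change on the final scale, as judged by the planned expert panel, or a standardised difference informed by the scoping review.
2. State that the pilot supplies only nuisance quantities: the post-test SD, preferably taken at a conservative upper limit such as the 80% confidence limit, and the correlation between the pre-test and the post-delivery score.
3. Size the between-group comparison for ANCOVA adjusted for the 36-week pre-test, and add ANCOVA to the methods under Data analysis.

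The cost is a few sentences, one additional question for the panel (whose stated task is to rate and discuss programme strategies) and a change to the listed analysis. The pre-test is already planned, so no new measurement is needed. The conservative SD raises the computed size by about 24% to 40% for pilots of 20 to 10 per arm. ANCOVA recovers part or all of that, depending on the pre-post correlation. That correlation is unknown, and because the two scores lie on either side of delivery it should be taken from the pilot with caution.
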